#### 9.1.4 Time windows for Study Visits

At each Study Visit, participants will be provided with their next scheduled appointment at QI CRF but can be seen up to one month before or one month after this date.

At the end of the study, eFI (electronic Frailty Index) scores will be requested retrospectively from the participant's GP (Annex 31). See Section 15.3.

Figure 6 below shows a summary of Phase 2.

| Participation                         | PHASE 2                                                                   |                      |                      |                      |                      |                      |                      |                      |                      |
|----------------------------------------------|----------------------------------------------------------------------------------|----------------------|----------------------|----------------------|----------------------|----------------------|----------------------|----------------------|----------------------|
|                                              | Baseline                                                                  | Study Visit 1 | Study Visit 2 | Study Visit 3 | Study Visit 4 | Study Visit 5 | Study Visit 6 | Study Visit 7 | Study Visit 8 |
|                                              | 0 months                                                                  | 6 months      | 1 year        | 1.5 years     | 2 years       | 2.5 years     | 3 years       | 3.5 years     | 4 years       |
|                                              |                                                                                  | 1 month either side  | 1 month either side  | 1 month either side  | 1 month either side  | 1 month either side  | 1 month either side  | 1 month either side  | 1 month either side  |
| Drop off stool sample at QJB                 | X                                                                                | X                    | X                    | X                    | X                    | X                    | X                    | X                    | X                    |
| Pick up stool collection pack for next visit | X                                                                                | X                    | X                    | X                    | X                    | X                    | X                    | X                    |                      |
| Cognitive Tests and related Questionnaires   | X                                                                                | X                    |                      | X                    |                      | X                    |                      | X                    |                      |
| Full Health Questionnaire                    | X                                                                                |                      |                      |                      |                      |                      |                      |                      |                      |
| Partial Health Questionnaire                 |                                                                                  | X                    | X                    | X                    | X                    | X                    | X                    | X                    | X                    |
| Blood Sample                                 | X                                                                                | X                    | X                    | X                    | X                    | X                    | X                    | X                    | X                    |
| Physical Measurement Collection              | X                                                                                |                      | X                    |                      | X                    |                      | X                    |                      | X                    |
| Optical Coherence Tomography (Retinal) Scan  | X                                                                                |                      |                      |                      | X                    |                      |                      |                      | X                    |
| Brain MRI (optional)                         | X                                                                                |                      |                      |                      |                      |                      |                      |                      | X                    |
| Electronic Frailty Index Data from GP        |                                                                                  |                      |                      |                      |                      |                      |                      |                      | X                    |
| Colonoscopy Tissue Biopsy                    | IF INVITED FOR A COLONOSCOPY AS PART OF THE NHS BOWEL CANCER SCREENING PROGRAMME |                      |                      |                      |                      |                      |                      |                      |                      |

Summary of Phase 2

Figure 6

## 10 Incidental Findings

During review of all results sent to the GP as detailed below, any clinically relevant incidental findings will be discussed with the participant by their GP.

### 10.1 Cognitive Tests

All cognitive tests and associated questionnaires will be sent to the participant's GP. Participants will be aware that the mini-ACE cognitive test is used as a tool in the clinical setting to diagnose dementia, but that it will only be used in combination with all other cognitive tests/associated questionnaires for research purposes. Copies of the mini-ACE and CCI test from the Pre-Study Visit will be sent to the participant's GP. The GP will also receive copies of cognitive tests and associated questionnaires taken at all the specified time points.

## 10.2 MRI Scans

[name] or a member of the Radiology team at NNUH will inform the Clinical Studies Officer at QIB of any incidental findings following the participant's MRI scan. The NNUH team will follow hospital standard procedures for incidental findings. The participant's GP will be sent a letter when a brain MRI scan has been performed (if applicable) along with a copy of the result.

## 10.3 OCT/OCT (A) Scans

[name] or a member of the Ophthalmology team will send a summary of the scan results which will include any incidental findings directly to the participant's GP. An anonymised copy will also be sent to the Clinical Studies Officer at QIB.

## 10.4 Full Blood Count, Biochemistry and Troponin C blood results

The Full Blood Count (FBC), Biochemistry and Troponin C samples will be analysed at the NNUH accredited Department Laboratory Medicine. The participant's GP will be sent a letter along with copies of all blood results at the appropriate time point.

## 10.5 Colonoscopy Biopsies

Any findings following routine care biopsies will follow the NNUH Trust policy.

# 11 STUDY PROCEDURES

The Schedule of Events is provided as Appendix A in Section 27.

## 11.1 Informed Consent

The PIS and Informed Consent Form will be presented to the participant at the Pre-study Visit detailing no less than the exact nature of the study; what it will involve for the participant; the implications and constraints of the protocol; the known side effects and any risks involved in taking part. It will be clearly stated that the participant is free to withdraw from the study at any time for any reason without prejudice to future care, without affecting their legal rights, and with no obligation to give the reason for withdrawal.

The participant will be allowed as much time as wished to consider the information, and the opportunity to question the Study Researcher, their GP or other independent parties to decide whether they will participate in the study. Written

informed consent will then be obtained using the Study Consent Form (Annex 10) by means of participant dated signature and dated signature of the Study Researcher. The Study Researcher obtaining informed consent will be GCP trained, be suitably qualified and experienced, have been authorised to do so by the Chief Investigator and will appear in the Delegation of Duties Log. A copy of the signed Informed Consent will be given/sent to the participant. The original signed form will be retained at the Sponsor site. A copy will be sent with the Summary PIS and the Full PIS to the participant's GP (Annex 21) and for insertion in to the participant's hospital notes along with the appropriate Full PIS. The Consent form will ask for explicit consent to have access to their GP and hospital notes for study-related activities.

Consent is an ongoing process and as such will be confirmed at each contact or visit by verbal means.

## 11.2 Informed Consent for Biorepository Storage

Following on from Informed Consent for study participation, the participant will be asked if they would be happy for the samples taken to be stored (anonymised) at -80° in the Norwich Biorepository during the study and after the end of the study. The Norwich Biorepository is a NNUH tissue bank where research samples taken as part of the study can be used by other researchers externally for future ethically-approved research. No additional samples will be taken for this purpose. The participant will be asked to read the current version of the NNUH Adult Tissue Bank Information Sheet and to sign this consent if they wish. This will be detailed in the PIS.

## 11.3 Study Specific Tests

### 11.3.1 Cognitive Tests

Cognitive tests are designed to measure memory, reasoning and thinking. This study is looking at the analyses of data and samples of participants who are deemed to be at low (no subjective and no objective cognitive deficit), medium (subjective but no objective cognitive deficit) or high (subjective and objective cognitive deficit) risk of developing dementia. Subtle objective cognitive deficits indicative of the prodromal stages of dementia are referred to as mild cognitive impairment (MCI) [26]. The MCI identifies currently healthy ageing individuals at high risk of

developing dementia. MCI does not mean a diagnosis of dementia as up to 40% of MCI patients revert back to healthy after 12 months.

In terms of diagnosing dementia in the clinical setting, there is no standardisation across the NHS. Most of the cognitive tests and associated questionnaires that will be used in this study are used in the clinical setting for diagnosing dementia, mainly the mini-ACE test, but there is variation in the use of these across dementia services nationally. The Full PIS states that the mini-ACE test is used in the clinical setting as a tool for diagnosing dementia, but for the purposes of this study, the mini-ACE, RCFT, CBI-R, PHQ 9 and TMT are used for recording different levels of cognition over time and are used in combination with each other only for the purposes of this research study and not for diagnostic purposes. See Section 15.1 for explanations of why individual cognitive tests and associated questionnaires are being used in this study.

Participants will be required to undergo a cognitive test (mini-ACE) and an associated questionnaire (CCI) following Informed Consent at the Pre-Study Visit. Final eligibility will be determined by [name] or his experienced Study Researcher/Research Assistant using pre-determined thresholds for each cohort as detailed below.

❖ Cohort 1 (low risk) - No subjective and no objective deficit = mini-ACE score of  $\geq 26/30$  and CCI score of  $< 16$  from the first 12 questions.

❖ Cohort 2 (medium risk) - Subjective and no objective deficit = mini-ACE score of  $\geq 26/30$  and CCI score of  $\geq 16$  from the first 12 questions.

❖ Cohort 3 (high risk) - Subjective and Objective deficit = mini-ACE score of  $< 26/30$  and CCI score of  $\geq 16$  from the first 12 questions.

For the purposes of this study, the high risk group will be referred to as having MCI.

Participants will then be assigned to one of the three cohorts based on these scoring thresholds. Results of the cognitive tests will not be discussed with participants as we do not wish to cause any undue anxiety or concern. Copies of completed cognitive tests and associated questionnaires will be sent to the participant's GP. Participants who do not fall within the threshold for that cohort, or if the appropriate cohort already has the maximum number of 120 participants, they will

be withdrawn from the study (see section 16). For any participant who is found to have an incidental finding of MCI, please see Section 10.1.

The NSFT Research Nurse team and the Study Researchers delivering the Cognitive Tests and associated questionnaires will have received full training from experienced Research Assistants.

1. Mini Addenbrooke's Cognitive Examination (Mini-ACE) [27] is a short 5 min standard cognitive screening test well validated and used in dementia (Annex 15.1).

2. Cognitive Change Index (CCI) [28], a validated self-completed measure of perception of the participant's cognitive decline (Annex 15.2). This will take approximately 5 mins.

In addition to the above, the following 7 Cognitive tests will also be performed at Study Visits 5, 7, 9 & 11:

3. Patient Health Questionnaire 9 (PHQ-9) [29], a validated, brief self-report multipurpose instrument for screening the severity of depression symptoms in the participant (Annex 15.3). This will take approximately 5 minutes.

4. Supermarket Task [30], a non-validated computer- and tablet-based assessment of spatial orientation using an ecological supermarket environment (Annex 15.4). This will take approximately 15 minutes.

5. Sea Hero Quest (SHQ), a non-validated novel computer, tablet, or virtual reality measure of spatial navigation within the context of a video game and takes 15 minutes to complete (Annex 15.5).

6. Cambridge Behavioural Inventory Revised (CBI-R) [31] is a validated self-rated measure of changes in the participant's behaviour. These domains include memory and orientation, everyday skills, self-care, abnormal behaviour, mood, beliefs, eating habits, sleep, stereotypic and motor behaviours and motivation and frequency of these behaviours (Annex 15.6). This takes around 15 minutes to complete.

7. The short version of the Body Perception Questionnaire [32], a non-validated, self-report questionnaire assessing the participant's degree of interoception ability (Annex 15.7).

8. The Rey Complex Figure Test (RCFT) [33], a validated short (10 min) measure of visual memory and visuospatial constructional ability which includes a 3-minute delayed recall (Annex 15.8).

9. The Trail Making Test (TMT) [34], a validated short (5 minute) test of processing speed, attention and set-switching (Annex 15.9).

### 11.3.2 Optical Coherence Tomography (OCT) Scans

There is a growing literature on the use of OCT scanning to measure both the Retinal Nerve Fibre Layer (RNFL) and the Inner Ganglion Cell Layer (iGCL) of the retina and correlating these measurements with the risk of dementia [17, 35]. Embryologically the eye is an out pouching from the brain and contains neural tissue. It is possible that if the brain is undergoing a degenerative atrophy as seen in dementia then there might also be measurable changes in the retina, particularly the retinal nerve fibres of the ganglion cells. This might mean that OCT of the RNFL or iGCL becomes a useful non-invasive way of detecting those at higher risk of dementia, or quantitatively measuring the response to novel treatment strategies. The OCT scan will be performed following the Baseline Visit, around Study Visit 4 and prior to Study Visit 8 in all participants. Consistent with this speculation is the very recent finding microvascular changes in the retina (foveal thinning) detected by using OCT angiography align well with imaging and biomarker evidence of preclinical Alzheimer's disease [36]. The OCT and retinal colour photo data collected will also detect age related macular degeneration and may allow us to correlate the presence or absence of AMD to the gut microbiome [37].

### 11.3.3 Optical Coherence Tomography Angiography OCT (A) Scans

We are also going to use the much newer technique of OCT (A) at the Baseline Visit & Visit 8 in subgroup 1 (the same 90 participants – 30 from each cohort who undergo a colonoscopy) which, in addition to the OCT scan, measures blood flow in the retina, again in a non-invasive manner. We wish to get OCT (A) scans on the participants in whom we have the most information about the gut microbiome and

this will be those in Subgroup 1. Ideally, we would wish to have OCT (A) in all participants but funding limitations mean this is not possible. In order to make meaningful conclusions from the OCT (A) data we need to compare participants from each cohort so arranging OCT (A) on the 90 participants in subgroup 1 seems a sensible compromise.

There is minimal data on correlating OCT (A) findings with dementia, or indeed how to quantify and analyse the large amount of data that OCT (A) scans generate [38].

However, the MOTION study is unique in providing an opportunity to collect OCT (A) data in ageing participants with and without MCI which will be examined by a masked observer to see if there is any change in the vascular pattern in participants at risk of developing dementia (cohort 3), looking at both the retinal and choroidal blood supply, measuring when possible the vascular density and looking for other changes such as enlargement of the foveal avascular zone which might reflect progressive microvascular changes.

#### 11.3.3.1 OCT (A) Scan Protocol

All participants recruited into the study will be offered a retinal OCT scan, colour photography and ophthalmic examination.

The following information will be collected: -

#### 11.3.3.2 History

- + Patient ID/Study number
- + Age
- + Ophthalmic history
- + Ophthalmic medication including vitamins to prevent age related macular degeneration
- + Any allergies

#### 11.3.3.3 Examination

- + Best corrected Visual acuity by ETDRS chart in each eye
- + Ishihara colour vision in each eye
- + Slit lamp examination
- + Intra-ocular pressure by Goldman Tonometry
- + Right eye (or left eye if right eye not suitable) will be dilated using tropicamide 1% eyedrop.

✚ Clinical examination of retina and optic nerve to pick up any confounding pathologies such as retinal vein occlusion, age related macular degeneration and glaucoma.

If participants decline dilating drops the examination will continue and we will document that they were not dilated in either eye.

#### 11.3.3.4 Investigations at every Ophthalmology visit

For all participants (n=360), acquisition protocol using SDOCT Spectralis OCT2 system will include the following methodology at the Baseline Visit, Study Visit 4 and Study Visit 8.

Retinal nerve fibre layer (RNFL) scans will be acquired with the standard peripapillary (pRNFL) scan pattern, at 100 frames Automatic Real-Time Tracking (ART) setting, by an OCT technician employing FOBMO (fovea to Bruch's membrane opening) axis orientation.

For all study participants, Posterior pole scans on glaucoma setting, will be used to obtain a 30 by 25 degree macular volume scan pattern, using 16 ART frames. This is a horizontal 61-line volume scan available as a standard OCT scan pattern on OCT2 system (with an interscan spacing interval of 120 microns). Built-in Spectralis (Heyex software version 6.9) will be used for automated retinal layer segmentation to report on the total retinal thickness, and individualized retinal layer thicknesses for ETDRS rings centred on the fovea and compared with available normative database. The individualized retinal layer thicknesses will be reported for RNFL (retinal nerve fibre layer), GCL (Ganglion cell layer), IPL (Inner Plexiform Layer), INL (Inner Nuclear Layer) OPL (Outer Plexiform Layer), OPL (Outer Plexiform Layer) and RPE (Retinal Pigment Epithelium Layer), as available with proprietary Heyex software (version 6.9 Heidelberg Engineering Ltd, Germany).

At all eye clinic study visits, Choroidal thickness will be measured using EDI (Enhanced depth imaging) cross-hair imaging at 100 ART frames setting. SFCT (sub-foveal choroidal thickness using the manual caliper between the two measurement points with the inner border at RPE and outer border at CSI (Chorio-scleral interface). Colour retinal photography of optic disc and Macula will be performed.

#### 11.3.3.5 OCT Angiography - OCT (A) scans

OCT (A) using Spectralis OCT2 system uses a centre wavelength of 870 nanometers with an A-scan frequency of 85,000 scans/s to obtain a volume at 6 microns spacing with a macular field of view of 3 \* 3 mm. Proprietary real time True track technology

is used by Heidelberg system, with 2-5 times B-scan repetition at the same retinal location to generate OCT (A) signal employing full-spectrum amplitude decorrelation software developed by the Heidelberg engineers. OCT (A) analysis will report on FAZ area (foveal avascular zone) using the built-in area measuring caliper, Vascular density indices of SCP (Superficial Capillary Plexus), ICP (Intermediate Capillary Plexus) and DCP (Deep Capillary Plexus).

Any scans of poor quality due to any reason, for example media opacity due to cataracts and less than Q (quality factor) of 20 will not be used for analysis.

#### 11.3.3.6 Main Outcome Measures

Peripapillary RNFL in superior, inferior, temporal and nasal quadrants and mean quadrants. Macular thickness will be recorded from the OCT and inner Ganglion cell layer thickness will be recorded by outer, inner and foveal segments.

Ishihara test score. Choroidal thickness will be recorded from the OCT. OCT (A) data will be analysed for area of Foveal Avascular Zone (FAZ).

Data reported from the right eye unless the OCT grader reports segmentation failure. In that case, data from the other eye will be used if no segmentation failure is recorded for that eye.

Participants with ophthalmic conditions which clearly interfere with the OCT measurements will be excluded from the analysis. This would include diabetic retinopathy, retinal vein occlusion, uveitis and glaucoma.

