|  |                                                                                                                  | 
Brain: The brain and cognitive impairment measured using a battery of cognitive tests at start of study (t=0) and at 6-monthly intervals up to 48 months.
 
Immune System: Immonocompetency determined by altered immune cell repertoires and effector function assessed using blood sampling at regular (6 month) intervals using various experimental protocols.
 
Eye: Structural changes including retinal nerve fibre layer thinning assessed by retinal scanning (OCT) at the start, mid-point and end of the study.
 
Metabolism: Metabolism and metabolic health assessed using faecal and blood samples obtained at regular (6-12 month) intervals.
 
Identifying change in virus (DNA/RNA), archaea and fungal populations from faecal samples obtained at regular intervals (6 months) throughout the study.
 |
|  | 
3: To determine if changes in the gut microbiota detected over time equally affect its different members?
 |                                                                                                                                                                                                                                                                                                                                                                                                                                                                                                                                                                                                                                                                                                                                                                                                                                                    |

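### The OCT eye-selection rule does not keep one eye across visits, so a participant's retinal change can be a difference between two eyes

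*Protocol*

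**What the plan says.** Section 11.3.3.6 of the protocol sets the default eye and the fallback: "Data reported from the right eye unless the OCT grader reports segmentation failure. In that case, data from the other eye will be used". The only condition on the fallback eye is that its own segmentation succeeded.

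Section 11.3.3.4 applies the acquisition protocol to all 360 participants "at the Baseline Visit, Study Visit 4 and Study Visit 8". The synopsis defines the eye outcome as change over time: "Structural changes including retinal nerve fibre layer thinning assessed by retinal scanning (OCT) at the start, mid-point and end of the study".

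Two neighbouring rules also act visit by visit or scan by scan:
- Section 11.3.3.3, on dilation: "Right eye (or left eye if right eye not suitable) will be dilated using tropicamide 1% eyedrop". It makes no reference to earlier visits, and participants may decline the drops.
- Section 11.3.3.5, on scan quality: scans with "less than Q (quality factor) of 20 will not be used for analysis". This removes a scan but does not say which eye is followed.

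No section says that the eye is chosen once per participant, that the Baseline eye is kept, or that change is computed only within one eye.

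**The concern.** The rule would serve an analysis of a single visit. It does not suit an outcome defined as thinning over four years. Suppose the right-eye scan is gradable at Baseline but fails at Visit 8, and the left-eye scan at Visit 8 is gradable. The rule then supplies the right eye at Baseline and the left eye at 48 months. The difference contains the standing difference between that person's two eyes as well as any true thinning. Question 8 in Section 19.1 relates change in the microbiome to change in clinical outcomes, so this extra variation would enter the outcome side of that analysis for the eye.

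**Working it through.** The protocol gives no SD, failure rate or power figure for OCT, so there is no stated figure to reproduce. The power table in Section 19.2 concerns MMSE change and is not affected.

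**Inputs from the protocol.** Three scan occasions. 300 participants expected at the end (Section 19.2). A 20% loss from 360 would leave 0.8 × 360 = 288; that is a separate inconsistency and barely alters the counts below.

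**Assumed inputs.**
- f: probability of segmentation failure per eye and scan, 1% to 10%, independent between eyes and visits.
- k: SD of the between-eye difference divided by the SD of within-eye four-year change, 0.5 to 3. The mean between-eye difference is taken as zero.

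**Step 1: how often change crosses eyes.** At a visit, P(right eye reported) = 1 − f and P(left eye reported) = f(1 − f). Among participants with both Baseline and Visit 8 usable,

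q = 2(1 − f)·f(1 − f) / [(1 − f) + f(1 − f)]² = 2f/(1 + f)².

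For f = 5%: 0.10/1.1025 = 9.1%. The expected number of crossed changes is 300 × 2f(1 − f)²; for f = 5%, 300 × 0.09025 = 27.

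**Step 2: variance of the change score.** Relative to same-eye change, the variance ratio is 1 + q·k².

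| f | q | Crossed, of 300 | Ratio, k = 0.5 | k = 1 | k = 2 | k = 3 |
|---|---|---|---|---|---|---|
| 1% | 2.0% | 6 | 1.005 | 1.02 | 1.08 | 1.18 |
| 2% | 3.8% | 12 | 1.01 | 1.04 | 1.15 | 1.35 |
| 5% | 9.1% | 27 | 1.02 | 1.09 | 1.36 | 1.82 |
| 10% | 16.5% | 49 | 1.04 | 1.17 | 1.66 | 2.49 |

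With 288 participants the crossed counts are about 6, 11, 26 and 47. For f = 5% and k = 2, 300 changes carry the information of 300/1.363, about 220.

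A switch somewhere among the three scans has probability 1 − (1 + f³)/(1 + f)³ when all three are usable: 2.9%, 5.8%, 13.6% and 24.8% for the four values of f.

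**Step 3: what a fixed eye costs.** If the study eye is set at Baseline and a later failure counts as missing, q = 0 and the ratio is 1. The additional Baseline-to-Visit-8 changes lost are 300 × f(1 − f)(1 − f²), which is 3, 6, 14 and 27 for f = 1%, 2%, 5% and 10%.

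For f = 5% and k = 2, the rule as written leaves 300 × 0.9975² = 298.5 usable changes, worth 298.5/1.363 = 219. The fixed eye leaves 300 × 0.9975 × 0.95 = 284 same-eye changes at full value.

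The two approaches break even at k = (1 + f)/√2, that is, k of 0.71 to 0.78 over this range of f. Below that the fixed eye loses slightly more than it gains; above it the fixed eye is better.

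**The case against.** **The unit is not stated.** Section 11.3.3.6 does not say whether the choice is made per scan, per visit or per participant. A reader might infer that the protocol expressly orders a scan-by-scan choice, but it does not. That reading follows from the trigger, which a grader records on a scan, and from the lack of any rule holding the eye fixed. A per-participant reading is possible but unwritten. This objection limits the point to what the rule permits.

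**Later plans could complete the rule.** Section 19.1 leaves the coding of outcomes to analysis plans registered before analysis, and one of these could add a same-eye rule. However, the protocol itself fixes the eye choice under its main OCT outcomes, and a plan that followed it faithfully would inherit the gap.

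**Switching may be rare.** Failure that persists in one eye means the other eye is used throughout, with no switch. Failures that occur in both eyes at once produce missing data instead. Section 11.3.3.6 also excludes several eye diseases that interfere with measurement. All of this stands and pushes the figures towards the low end.

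**Dilation.** A reader might infer that the fallback eye is always the undilated one. The protocol does not support that: Section 11.3.3.3 allows the left eye to be dilated when the right is unsuitable, and participants may decline drops. At most, the fallback eye may be undilated when failure in a dilated right eye is found only at grading.

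**Bias between cohorts.** A reader might infer a biased cohort comparison. That would need a mean right-left difference and a net direction of switching that differs between cohorts. The documents give neither, and in the model above switches in the two directions are equally likely.

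**Conclusion.** The point holds in a limited form. The protocol states an eye-selection rule that permits a cross-eye change score for an outcome defined as change, and no section prevents it. On assumed failure rates of 1-10%, independent between eyes and visits, about 2-17% of usable Baseline-to-Visit-8 changes would cross eyes. The variance ratio then runs from 1.005 to 2.49, depending mainly on a between-eye SD that the documents do not give. When that SD is half the SD of within-eye change, the effect is negligible (at most 1.04).

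The consequence is added noise in a secondary outcome. The primary objective on microbiota composition, the MMSE power calculation and single-visit OCT analyses are untouched. The repair is cheap enough to make before OCT change is analysed.

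**What to change.** Amend Section 11.3.3.6 for longitudinal analyses to say:
- Each participant has one study eye, chosen at Baseline and blind to cohort: the right eye if gradable, otherwise the left.
- That eye is used at all visits. A later failed scan in it is treated as missing, with no later swap to the fellow eye.
- Change is never computed across eyes.

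Alternatively, where both eyes are scanned, analyse all gradable eye-visits in a mixed model with eye nested in participant. This avoids most of the loss shown in step 3. It needs Section 11.3.3.4 to state that both eyes are scanned, which the fallback rule presupposes but that section does not say.

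The existing rule can stay for cross-sectional analyses. The amendment takes a few sentences and no new scans. Its price under the fixed-eye option is a few missing eye-visits: on the assumptions above, about 3 to 27 of 300 Baseline-to-Visit-8 changes.
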